**C.3. Measures**

**C.3.a. Objective physical activity measurement.** Within two weeks of their baseline assessment all participants will come in to complete the consent and be fitted with a blinded pedometer with instructions on placement and wear. Participants will be instructed to wear the device for the 7 days prior to their baseline visit. All pedometers will be blinded to minimize behavior change in response to the assessment. Logs will be collected at the baseline visit. Log data will be used to determine days and hours of wear. At the baseline visit, pedometers will be collected and data will be downloaded to the study computer and processed using manufacturer software. Participants will also be provided with an accelerometer during this period for assessment of total physical activity levels. Participants will also provide objective physical activity data at follow-up as outlined below.

**C.3.a.1 Pedometer.** We will use the Omron HJ 720IT pedometer in this study. This pedometer displays seven days of step count data (when not blinded and sealed), but can store up to 41 days of step count data in the memory for later download. Research has suggested that the Omron pedometer technology may have superior accuracy among elderly and obese individuals.^119, 120^ Given the high prevalence of obesity in the general population^121^ and the age range of our eligibility criteria, we believe it is prudent to use the Omron device. Participants will complete logs and record daily hours of wear.

**C.3.a.2. Accelerometer.** We will use the Actigraph brand accelerometer in this study. The accelerometer will allow us to estimate the participants’ total physical activity level including minutes of moderate or vigorous intensity physical activity as well as a summary indicator of physical activity that accounts for both intensity and duration, expressed as metabolic equivalent (MET) minutes per week. Finally, it will allow us to estimate the participants’ energy expenditure.

Accelerometers are generally recognized as a “gold-standard” approach for the objective measurement of physical activity. Accelerometers record the g-forces common to movement and translate them into data that reflect the frequency and intensity of movement, sampled at set intervals. With accelerometry the duration time spent at defined intensities of activity can be determined, which allows for the more valid assessment of physical activity. In interventions of physical activity behavior change, accelerometers provide the most valid estimates of change in energy expenditure.

**C.3.b. Physiologic assessment.** At the baseline and follow-up visit, all participants will undergo a fasting blood draw. Staff will also measure participants’ weight and height.

**C.3.b.1. Serum marker measurement.** Blood will be collected after a 12 hour fast. Participants will also be instructed not to consume alcohol for 18 hours prior to the blood draw or take NSAIDs for 24 hours prior to blood draw. Because daily physical activity is part of the intervention message, participants will not be asked to terminate physical activity, but limit it. Specifically, participants will be asked not to participate in vigorous physical activity for 12 hours prior to the blood draw and not to participate in any moderate or vigorous intensity physical activity for three hours prior to the blood draw.

The Center for Clinical Studies (CCS) will oversee the physiologic assessment, including sample collection, processing, and storage. Samples will be processed in order to allow subsequent analysis of levels of insulin, C-peptide, IL-6 and PGE-2. Blood will be processed and stored as serum, EDTA plasma, and red blood cells. Each participant’s baseline and follow-up blood samples will be assayed in the same batch. In addition, an equal number of samples from each study arm will be included in each batch.

**C.3.b.2. Body composition assessment.** Body weight and height will be measured in duplicate using a digital scale and tape measure constructed specifically for research quality measures. We will also measure waist and hip circumference.

**C.3.c. Questionnaire.** Following the physiologic assessment and pedometer return, participants will be provided a questionnaire that includes physical activity, potential confounder and sociodemographic information. Measures are summarized in Table 2 and are described in detail below.

**C.3.c.1. Self-reported physical activity.** As a supplement to the step count data, participants will complete a physical activity questionnaire. We will use the Paffenbarger Physical Activity Questionnaire (PPAQ) which assesses moderate and vigorous intensity physical activity with distinct items to measure walking.^95, 122^ The PPAQ also allows measurement of both leisure time only and total (leisure time plus occupational and transport) physical activity. This validated instrument was selected because it provides an assessment of total physical activity while also employing several detailed walking items. The information in the PPAQ supplements that provided by the accelerometer and pedometer by providing information about context/domain of physical activity.

**C.3.c.2. Modifying mechanisms.** We will also collect information related to the intervention constructs using validated published scales whenever possible. Self-efficacy for physical activity will be measured using the Exercise Confidence Survey.^123^ Social support for physical activity will be measured using the Sallis Social Support Scale.^124^

| **Table 2. Survey measures** | | |  |  |
| --- | --- | --- | --- | --- |
| **Construct** | **Measure** | **Baseline** | | **Follow up** |
| Self-reported physical activity | Paffenbarger Questionnaire | X | | x |
| Sociodemographic | Age | X | |  |
|  | Marital Status | x | |  |
|  | Race/ethnicity | X | |  |
|  | Gender | X | |  |
|  | Education | X | |  |
|  | Income | X | |  |
|  | Occupation | X | |  |
|  | Immigrant status | X | |  |
| Other cancer risk factors | Family history of colorectal cancer | X | | x |
|  | Current and past tobacco use | X | | x |
|  | Hormone use (women only) | X | | x |
|  | Diet (Willett Questionnaire) | X | | x |
| Self efficacy | Exercise Confidence Survey | X | | x |
| Social support | Sallis Social Support Scale | X | | x |
| Neighborhood safety | Day/Night; Home/work | X | | x |
| Benefits of physical activity | HINTS questions | X | | x |
| Neighborhood walkability and access | IPAPS self administered module | X | | X |
| Length of residence |  | X | |  |
| Perceived neighborhood disorder |  | X | | X |
| Depression | CES-D | X | | X |
| Perceived Stress |  | X | | X |
| Coping strategies | Brief COPE | X | | X |
| Urban life stress | Urban Life Stress Scale | X | | X |

**C.3.c.3. Other factors potentially related to physical activity**. We will measure the perceived benefits of physical activity using the HINTS survey items.^125^ This instrument asks participants: (1) As far as you know, does physical activity or exercise increase the chances of getting some types of cancer, decrease the chances of getting some types of cancer, or does it not make much difference? (2) Can exercise help to lower the chances of getting some types of cancer or does exercise not make much difference? We will also administer the International Physical Activity Prevalence Study environmental module which queries participants about their neighborhood and its walkability as well as access to physical activity and recreation facilities. We will assess perceived neighborhood safety by asking participants, “how safe is the neighborhood you live in during the daytime?” We will also ask about the safety of the neighborhood they live in at night and the neighborhood they work in. Response options will be “safe”, “a little unsafe” and “not at all safe”. In previous work by the research team, these questions were associated with daily step count.^126^ Additional items on stress ^127-131^, neighborhood environment ^132, 133^, depression^134^, and coping mechanisms^135^ will also be included on the questionnaire.

**C.3.c.3. Other measures.** The baseline and follow-up questionnaires will also query sociodemographic variables (age, race/ethnicity, gender, education, household income, current occupation), family history of colon cancer, current and past tobacco use, diet and supplement use (using the Willett food frequency questionnaire) and use of hormones (in women).

**C.4. Randomization.** Following the baseline assessment, study staff will assign participants to an intervention condition using a random numbers program. An equal number of individuals will be assigned to each condition (10 low dose, 10 high dose). Staff doing the randomization will not participate in the eligibility screening or baseline assessment and will not have access to information about participants.

**C.5. Intervention.** Following the baseline assessment, participants will be randomly assigned to one of two doses of physical activity delivered through the First Step program.

**C.5.a. First Step Program.** The First Step Program (also published as Manpo-Kei^111^) is a theoretically-based two phase intervention that aims to promote adoption of physical activity, specifically walking, and adherence to the newly adopted behavior.^112^ The program draws on social cognitive theory and the Transtheoretical Model of behavior change. The first phase lasts one month and is comprised of four weekly facilitated group meetings. The group meeting covers individual progress reports, brief group walk of increasing duration, group strategy discussion, and individual goal setting for the following week. Participants use pedometers and logs to monitor their progress. Between the weekly sessions, participants wear pedometers to monitor their daily steps. Participants log their goals and daily step counts. The program addresses self-efficacy, outcome expectations and social support in line with social cognitive theory and moves participants through the phases (precontemplation, contemplation, preparation, action and maintenance) of the Transtheoretical Model. In the second phase, lasting eight weeks, participants receive weekly phone contact. The First Step Program aims to progress participants to a steps per day goal. The First Step Program has successfully increased physical activity in several diabetic patient populations.^136, 137^ The First Step Program has resulted in significant changes in waist girth.^137, 138^ Studies have found mixed results for changes in weight.^137, 138^ Changes have not been seen for waist to hip ratio^137^, or insulin.^136^.

**C.5.b. Dose.** To date, the First Step Program has administered a single dose recommendation of 30 minutes of walking and 10,000 steps per day. This is in line with the current federal physical activity guidelines for health.^6^ Research in colon cancer survivors suggests that 60 minutes of physical activity is needed to prevent recurrence and improve survival. This is also the amount of activity indicated as necessary to maintain a healthy weight. Thus, we will compare the First Step Program as previously delivered in diabetics, with a modified version that delivers a higher dose of physical activity (60 minutes of walking, 13,000 steps per day).

**C.6. Intervention evaluation and outcome measurement**

**C.6.a. Objective physical activity.** One week prior to the conclusion of the study, participants will come into receive a blinded sealed pedometer to wear for seven days. Participants will again be given an Actigraph device to wear for seven days. At the end of the seven day period, all participants will return to Washington University for their study conclusion evaluation visit. Data from the devices will be processed as at the baseline visit. Participants will complete a questionnaire and undergo a final physiologic examination and blood draw.

**C.6.b. Physiologic measures.** Participants will undergo physiologic measurement identical to baseline at the end of the study. We will measure height and weight, as well as insulin, C-peptide, IL-6 and PGE-2 levels. Blood will be processed and stored as serum, EDTA plasma, and red blood cells.

**C.6.c. Questionnaire.** Following the physiologic assessment and pedometer return, participants will be provided a questionnaire identical to that used at baseline that includes items querying physical activity, potential confounder and sociodemographic information.

**C.7. Incentives.** All study participants will receive $50 each for completing the baseline assessment as well as $50 for attending the 3 month (study end) visit. Participants will also be allowed to keep their study pedometers.

**C.8. Retention strategies.** To ensure high retention rates of study participants, we will employ several strategies including providing detailed information on risks associated with study participation to build trust, accessing participant information through their physician to help reinforce the clinical support for the study program, and the use of incentives. In addition, at enrollment we will collect multiple sources of contact information from participants including home, work and mobile phone numbers as well as email addresses where available. We will also request the name and contact information for a friend or family member who can be contacted in the event the participant relocates. Our regular phone contact will help participants feel connected to and invested in the study.

**C.9. Sample size and power considerations for primary outcomes.** Schmitz et al found baseline insulin in the control group to be 4.46 (+/- 0.59) uU/ml and in intervention subjects to be 5.18 (+/- 0.54) uU/ml in an exercise study.^67^ Over 39 weeks of exercise intervention, insulin increased an average of 1.16 uU/ml in the control group and 0.05 uU/ml in the intervention group, for a net intervention effect of 1.1 uU/ml. Using this data, the sample size to achieve 85% power for the primary comparison of insulin change over 12 months between the intervention and control groups using a Bonferroni correction with two-sided 0.05/2 = 0.025 and an estimated correlation over 39 weeks for insulin of 0.5 is n = 2σ^2^_change_ (Z_0.9875_ + Z_0.85_)^2^/ Δ^2^

where σ^2^_change_ = 2 σ^2^_baseline_ (1 – ρ) = 123.63, σ^2^_baseline_ = 0.59^2^, ρ = 0.5, Z_0.9875_ = 2.24, Z_0.85_ = 1.035, and Δ = 1.1 This yields a sample size of 6 subjects per group.

The estimates of change for insulin are comparable to the difference between the highest and lowest quintiles of physical activity in the Nurses’ Health Study (difference = 1.37 μU/ml) and the Health Professionals’ Follow-up Study (difference = 2.4 μU/ml).^68^ The difference in C-peptide between highest and lowest quintile of physical activity among women in the Nurses’ Health Study was 0.44 ng/mL. The mean level at baseline was 1.92 +/- 0.91 ng/mL. In the Health Professionals Follow-up Study, the within person correlation for C-peptide over four years was 0.57. This yields a sample size of 79 subjects per group. We can assume the within person correlation over one year is higher. If the correlation rises to 0.73, the sample size is 50 subjects per group.

In a 12-week exercise study of lean men, Dekker et al reported a mean IL-6 level of 2.8 +/- 0.6 pg/mL at baseline and of 1.9 pg/mL at study end for a mean change of 0.9 pg/mL.^87^ Assuming a correlation of 0.85, this yields a sample size of 3 subjects per group. If the correlation drops to 0.5, the sample size increases to 10 subjects per group.

Thus, based on our estimates, we estimate that 20 subjects per group is sufficient to detect differences in several of our outcomes, but not all. 50 subjects per group will provide sufficient power to detect differences in all our markers. However, as this is a pilot project we are not concerned with obtaining sufficient power in our outcomes and we will enroll 20 subjects (10 per group). We realize that participant drop out may prohibit our ability to detect differences in some outcomes, but as noted above, **this is a pilot feasibility study**.

**C.11. Data analysis**.

**C.11.a. Primary Aim:** To conduct a dose response pilot trial of low (30 min/day) or high (60 min/day) dose exercise in men and women at increased risk of colon cancer. The major outcomes are changes in serum levels of four risk-related biomarkers: insulin, C-peptide, IL-6 and PGE-2.

Hypothesis 1.1: First we will evaluate randomization success by comparing the two intervention groups on demographic and health factors. We will then evaluate intervention effects by differences in biomarker levels at study end between intervention groups using linear regression. We will compare differences in mean change in each of the biomarkers from baseline to three months between intervention groups. The analysis is based on change over three months using mixed effects regression models with PROC MIXED of SAS. The model is:

Y_it_ = α + β_1_t + β_2_X_i1_ + β_3_X_i1_t + β_4_tY_i0_ + e_it_

where Y_it_ = biomarker for subject i at time t, where t = 0 for baseline, t = 1 for 3 months.

X_i1_ = 1 if i^th^ subject is in the Plus intervention group, = 0 otherwise; e_it_ ~ N(0, σ^2^)

Of primary interest is β_3_ = mean difference in biomarker level change between intervention groups. The coefficient β_2_ allows for mean differences in level between groups at baseline. The coefficient β_4_ allows the change in biomarker to depend on initial level. We will conduct unadjusted analyses because of the randomization design but will also examine the effects of adjusting for sociodemographic factors, and family history of colon cancer. We will conduct outcome analyses based on assigned treatment at randomization regardless of adherence (intent to treat analysis). Throughout our analyses missing data will be imputed.^139^

**C.11.b. Secondary Aim: To compare changes in the secondary outcome of physical activity over three months.**

Hypothesis 2.1: We will evaluate the intervention effectiveness at changing physical activity levels by comparing change in average step count recorded on blinded pedometers from baseline to follow up between the intervention groups. Mixed effects regression will be used to account for the longitudinal design. The outcome variable will be the average steps per day for the measurement period. The measurement period at baseline and follow-up is the seven day period participants were required to wear the blinded pedometer. Only days where the participant wore the pedometer for at least eight hours will be counted and the average will be based on the number of full days of wear. The analysis is based on change using mixed effects regression models similar to that outlined in Aim 1. We will also examine the percentage of intervention participants meeting the 10,000 and 13,000 steps per day goals at the study conclusion based on data recorded on the pedometer. We will use the last seven days of the phase. We will also examine the percent of participants adhering to their study arm prescription (defined as completing 90% of required physical activity) at three months. We will examine whether sociodemographic factors, overall physical activity level, or family history of colon cancer are associated with meeting the intervention step count requirement. Finally, we will examine whether the intervention changed total physical activity levels by comparing baseline and follow-up total physical activity levels (as measured by the PPAQ) in the intervention groups and by comparing change in those levels between the intervention groups using the general estimating equation modification to linear regression.

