**A.5.c. The 10,000 Steps Per Day Goal:** For pedometers to be successfully implemented in physical activity promotion interventions, they must be paired with clear and empirically-meaningful step count recommendations. The 10,000 steps per day recommendation has become increasingly popular with the public, media, and interested corporations (including recent marketing efforts by McDonald’s and Kellogg cereals).^107^ Existing pedometer-based physical activity promotion studies have also adopted this intervention message. While there has been empirical support for the 10,000 steps per day goal in clinical and monitored populations,^101, 108, 109^ the goal may initially be too ambitious for sedentary and older adult populations, who may take as few as 3,500 – 5,500 steps per day.^101^ A 10,000 steps per day goal for these individuals then, amounts to a two- to three-fold increase in daily physical activity – a recommendation that is very likely to promote attrition.^110^ Given that there is some evidence to suggest that a single 10,000 steps per day goal may in fact be an ineffective physical activity promotion strategy, particularly among the largely sedentary populations who could benefit most from increases in their physical activity patterns, interventions that employ stepwise physical activity goals and incorporate other ways of promoting physical activity in addition to step count recommendations may be most effective.

1. **SPECIFIC AIMS**

To design and evaluate the feasibility of a pilot version of a colon cancer prevention intervention focused on walking. Individuals (n=20) with a polyp found on screening colonoscopy in the last six months (i.e., a colonoscopy to detect polyps or adenocarcinoma) will be enrolled and randomized to an evidence-based intervention recommending one of two physical activity recommendations (30 or 60 minutes). Participants in both conditions will receive the First Step intervention, which has previously been tested and found to be efficacious for increasing physical activity in clinical populations. First Step recommends walking most days of the week using a daily step count goal to monitor and motivate behavior change.^111, 112^ Outcomes will be measured at one month and three months post baseline. We anticipate larger changes in the primary outcomes in the Plus group than the standard intervention group.

Primary Outcomes: Blood levels of insulin, C-peptide, IL-6, and PGE-2

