**Additional Exclusion Criterion: NSAID use.** Participants who are regular NSAID users will be excluded as this may interfere with the measurement of inflammatory marker outcomes. Regular use is defined as taking 80mg or more per day of aspirin, ibuprofen, naproxen or other NSAID 5 or more days of the week.

**Additional Inclusion Criterion: Sedentary.** Individuals who report 30 or more minutes of moderate intensity physical activity five or more days per week or 20 or more minutes of vigorous intensity physical activity three or more days per week will be considered physically active and thus, ineligible. Participants will be administered the Behavioral Risk Factor Surveillance System (BRFSS) physical activity questionnaire as it is a brief screening tool useful for this purpose. This instrument asks participants to report on physical activity of at least moderate intensity performed in bouts of at least 10 minutes during the previous week. Individuals who report having been diagnosed with Type 1 or Type II diabetes will be included.

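### C.11.b treats a before-after change in self-reported activity as evidence that the programme changed activity, although no arm goes without the programme

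*Protocol*

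**What the plan says.** The last analysis listed under the secondary aim (protocol C.11.b) concerns total physical activity. The protocol states that "we will examine whether the intervention changed total physical activity levels by comparing baseline and follow-up total physical activity levels", with total activity "as measured by the PPAQ) in the intervention groups". The same sentence gives a second route to the same question: "by comparing change in those levels between the intervention groups using the general estimating equation modification to linear regression".

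On the design, the Specific Aims section says that "Participants in both conditions will receive the First Step intervention", and C.5 says that "participants will be randomly assigned to one of two doses of physical activity delivered through the First Step program". There is no untreated or delayed arm.

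On entry, C.2.b screens with the BRFSS questionnaire, which asks about "physical activity of at least moderate intensity performed in bouts of at least 10 minutes during the previous week". People above the stated thresholds "will be considered physically active and thus, ineligible". The PPAQ is a different instrument, completed later, at the baseline visit (C.3.c, C.3.c.1).

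**The concern.** The sentence attaches a causal question, whether the intervention changed activity, to a comparison that has no control. Everyone in the before-after comparison receives the programme, so anything else that moves reported activity over the 12 weeks is counted as programme effect. Two such influences need no special conditions. One is season. The other is reporting: the PPAQ is unblinded self-report, completed by people who have been coached, contacted weekly and asked to log their steps (C.5.a). The blinded pedometer, which guards the main secondary analysis against behaviour change in response to measurement, is not the measure used here.

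The between-arm comparison in the same sentence does not fill the gap. It compares the 60-minute with the 30-minute prescription and says nothing about the programme against no programme. Followed as written, the plan allows a report that First Step changed total activity when the design cannot support that statement. It is also the kind of statement that a later, larger trial might cite.

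**Working it through.** The protocol gives no effect size, standard deviation, correlation or significance level for the PPAQ comparison, so there is no stated figure to reproduce. The calculations below are illustrations on assumed inputs.

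**1. What each comparison estimates.** Let d be the change that would occur without the programme, and let e30 and e60 be the programme effects at the two doses.
- Within the 30-minute arm: d + e30
- Within the 60-minute arm: d + e60
- Pooled, with equal arms: d + (e30 + e60)/2
- Between arms: (d + e60) − (d + e30) = e60 − e30

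The first three all contain d, and no arm estimates d alone. The fourth is free of d as far as d is common to both arms.

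**2. How often drift alone would look like a change.** Assumptions: no programme effect; all 20 participants (C.9) pooled; two-sided 5% paired t test; repeat correlation ρ; drift expressed in SDs of the PPAQ measure.
- SD of change = √(2(1 − ρ)). At ρ = 0.5 this is √1 = 1.
- Noncentrality = drift × √20 / SD of change; 19 degrees of freedom; critical value 2.093.
- Drift 0.25 SD, ρ = 0.5: noncentrality 0.25 × 4.472 = 1.118, probability of significance 0.186.
- Drift 0.5 SD, ρ = 0.5: noncentrality 2.236, probability 0.565.

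| ρ | drift 0 | drift 0.25 SD | drift 0.5 SD |
|---|---|---|---|
| 0.3 | 0.05 | 0.146 | 0.434 |
| 0.5 | 0.05 | 0.186 | 0.565 |
| 0.7 | 0.05 | 0.278 | 0.782 |

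**3. The low-activity screen.** Assume that 75% of people fall below the screen, borrowing the share that section A gives for failing to meet recommended activity levels. Assume also a normal distribution.
- Mean of those selected = −φ(0.674)/0.75 = −0.318/0.75 = −0.424 SD.
- Expected rise with no programme effect = 0.424 × (r1 − r2), where r1 is the correlation of the screen with baseline and r2 its correlation with three months.
- If r1 = r2, the rise is 0.
- If r1 lies in 0.6 to 0.8 and r2 in 0.3 to 0.5, the rise runs from 0.424 × 0.1 = 0.042 to 0.424 × 0.5 = 0.212 SD.

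Allowing for equal correlations, the range is 0 to about 0.21 SD. At ρ = 0.5 and n = 20, a rise of 0.042 to 0.212 SD is significant in 5.4% to 14.7% of trials, against 5% nominal. The screen is thus a possible small contributor and not the main mechanism.

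**The case against.** The strongest reply is that little rests on this analysis. It comes last under a secondary aim, and C.3.c.1 collects the PPAQ to supplement the step counts. Hypothesis 2 is a comparison of doses. The declared test of effectiveness in C.11.b is the between-arm change in blinded-pedometer steps, and the primary parameter in C.11.a is the between-arm coefficient β3. A pilot may also reasonably ask whether people in both arms became more active, which the between-arm contrast cannot show if both rise equally. All of this stands. It sets the weight of the point and is the reason to keep the within-arm estimates. It does not justify the causal wording.

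It is also fair that the protocol names no paired test, level or decision rule for this comparison, and that the drift sizes are assumed. The percentages show sensitivity and are not forecasts. The seasonal part would partly average out if enrolment were spread over the year.

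Three stronger readings may tempt a reader, and the documents do not support them.
- **That the screen by itself pushes later reports upward.** Screening and baseline use separate instruments at separate times. A rise follows only if the screen correlates more strongly with baseline than with follow-up.
- **That each arm will be tested separately, and significance in one arm only will be read as a dose effect.** The protocol does not say so. A single longitudinal model fits the sentence equally well.
- **That the planning study in C.9 demonstrates this error.** There, "insulin increased an average of 1.16 uU/ml in the control group and 0.05 uU/ml in the intervention group". A before-after reading would have hidden a controlled effect, not created a false one, and the outcome was insulin over 39 weeks, not self-reported activity over 12.

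**Conclusion.** The point holds, at minor severity. C.11.b presents a within-group before-after PPAQ comparison as one of two ways to learn whether the intervention changed total activity, and with First Step given to both arms that inference is not available. This conclusion rests on the design alone and needs none of the assumed numbers.

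The size of the risk does depend on assumptions. With a pooled test of 20 people and ρ = 0.5, drift of 0.25 or 0.5 SD would be significant in 18.6% or 56.5% of trials. Over ρ = 0.3 to 0.7 the ranges are 14.6% to 27.8% and 43.4% to 78.2%. The screen could account for about 0 to 0.21 SD of such drift.

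A reader might infer that the trial's conclusions on activity or biomarkers are generally compromised. They are not: the primary biomarker contrast and the blinded-pedometer contrast are between arms, and common drift cancels in both. The between-arm PPAQ contrast shares that protection, although reporting that differs between the arms would remain in it.

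**What to change.** In C.11.b, stop using the baseline-to-follow-up PPAQ comparison to decide whether the intervention changed total activity. Report the mean within-arm changes with 95% confidence intervals as descriptive, and state that they cannot be attributed to the programme because no arm goes without it. Let the between-arm difference in change carry the only effect claim, worded as the 60-minute versus the 30-minute prescription.

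The cost is a change of wording, with no new data, visits or participants. The downside is that the sponsor gives up a causal statement about the programme as a whole.
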